##### Reported functioning

Data from this domain are obtained from four questionnaires sent to patients and filled up by them via internet. All the questionnaires require 10–15 minutes to be filled in.

*Physical functioning* (*Rand36 Physical Functioning subscale—Rand36-PF*). The Rand36 is a health-related quality of life survey that measures the impact of health on patients’ well-being and ability to function. Patients are asked to answer only the Physical Functioning (PF) subscale which looks at the limitations patients experience during their daily activities. Each of the 10 items belonging to the PF subscale has a three-level response choice ranging from 0 (limited a lot) to 100 (not limited at all), the total average score ranges from 0 to 100 too; where a higher score is associated with a greater limitation in performing daily activities. For the purposes of the study, the Dutch translation of the Rand36 is used, which has shown good internal consistency (Cronbach’s α=0.92) and test–retest reliability (r=0.72–0.82) in the general population.^73 74^

*Disability* (Pain Disability Index—*PDI*). The index is a 7-item questionnaire which measures the interference of pain with the ability to function in different daily life activities: family/home responsibilities, recreation, social activity, occupation, sexual behaviour, self-care and life support activity. Each item ranges from 0 (no interference) to 10 (total interference), and the total score ranges from 0 to 70; where scoring higher is associated with higher interference in daily life activities. The PDI has shown modest test–retest reliability (r=0.44) and high internal consistency (Cronbach’s α=0.86) in patients with chronic pain.^75^ For the purposes of the study the Dutch translation of the PDI is used, which has shown a good internal consistency (Cronbach’s α=0.85) and test–retest reliability (ICC=0.76) in patients with musculoskeletal pain.^76^

*Work ability* (*Work Ability Score—WAS*). The score is a single-item question which compares patient’s current work ability with their lifetime best. The result is a score ranging from 0 (unable to work) to 10 (best working ability). The single-item question is part of the Work Ability Index (WAI), a questionnaire which measures work ability and has shown to be test–retest reliable (difference between test and retest=−0.53) in construction workers.^77^ The WAS has shown to be highly correlated to the 28 items of the WAI among women on a long-term sick leave (r=0.87)^78^ and among active workers (r=0.63).^79^

#### Supplementary measurements

##### Demographic characteristics

Patients fill in a form with their details when the QST assessment takes place. Such details include: age, sex, nationality, height, weight, pain characteristics (affected body area, duration and medication, if applicable), educational level and employment characteristics (work status and physical work demands per Dictionary of Occupational Titles).^80^

##### Pain-related questionnaires

*Pain intensity* (*Visual Analogue Scale—VAS Pain*). The scale is a single-item question to assess the current pain intensity in adults. It is a straight line with ‘no pain’ (score=0) at one end and ‘pain as bad as it could be’ (score=100) at the other, in which patients are asked to mark the line at the level that represents their pain level. The score is the distance between the mark and the ‘no pain’ end, where scoring higher is associated with greater pain intensity. The VAS Pain has shown good validity (r=0.62–0.91) and good test–retest reliability (literate r=0.94 and illiterate r=0.71) in patients with rheumatic pain conditions.^81^ VAS Pain is sent to patients and filled in by them via internet along with the battery of functioning questionnaires (described above), that is, at baseline and weekly during the interdisciplinary rehabilitation programme.
*Body response to a straining exercise* (*Pain Response Questionnaire—PRQ*).^82^ The questionnaire assesses the pain intensity of the different body locations on an 11-point numeric scale (NRS) ranging from 0 (no pain) to 10 (worst pain imaginable), and the type of pain felt (muscle soreness, other, both or unknown). Additionally, it controls for the use of medication and for the performance of any other strenuous PA. For the purposes of this study, the body locations measured are predefined to four and the questionnaire is being filled in on three occasions: before the CPET, immediately afterwards and 24 hours later. PRQ is filled up at the same moment when the aerobic capacity test is performed (ie, during baseline and discharge assessments).

##### Psychological screening questionnaires

These questionnaires measure psychosocial features common to CSS that have demonstrated to affect pain experience and functioning.^83^ Patients fill in the questionnaires via internet that are sent per CAU procedures by the Pain Rehabilitation team. Such questionnaires include:

*Pain Catastrophizing Scale* (*PCS*). The 13-item questionnaire measures in a 5-point Likert scale (0—not at all, 4—all the time) the degree to which patients have had catastrophic thoughts or feelings during their pain experience and accounts for three subscales or dimensions: rumination, magnification and helplessness.^84^ For the purposes of the study the Dutch translation of the PCS is used,^85^ which has shown good internal consistency (Cronbach’s α=0.85–0.91) and test–retest reliability (r=0.92) among healthy individuals (students) and patients with CLBP.^86^

*Injustice Experience Questionnaire* (*IEQ*). The 12-item reported questionnaire assesses in a 5-point Likert scale from (0—never, 4—all the time) four different aspects of the perceived injustice due to injury: severity, blame, unfairness and irreparability. The questionnaire has shown to have good internal consistency (Cronbach’s α=0.92) and test–retest reliability (ICC=0.98) in a group of patients with fibromyalgia.^87^ For the purposes of the study the Dutch translation of the IEQ is used, as translated by the Pain in Motion group.^88^

*Brief Symptom Inventory* (*BSI*). The inventory is a 53-item reported questionnaire which assesses patient’s current level of psychological distress with 5-point Likert scale questions (0—not at all, 4—extremely), the amount of symptoms present and their severity.^89^ BSI is composed of nine subscales: somatisation, obsession-compulsion, interpersonal sensitivity, depression, anxiety, hostility, phobic anxiety, paranoid ideation and psychoticism. For the purposes of the study the Dutch translation of the BSI is used, which has shown good internal consistency (Cronbach’s α=0.71–0.87) and test–retest reliability (r=0.71–0.89) among psychiatric outpatient and healthy individual groups.^90^

### Sample size

Due to the limited amount of relevant previous or similar studies, the sample sizes for the several analyses described in this research protocol are estimated a priori with GPower (G*Power for Windows, Version 3.1.9.2), and are exploratory as a result.

The following sample size calculations, as well as the planned statistical analyses later described, will be performed with proxies for the main variables. Additionally, due to the influence of patient’s sex and age in the assessment outcomes, all analyses will include these variables for a moderator effect.

*Sample size for objective 1: to analyse the association between instruments assessing reference symptoms and signs attributed to CS.* Correlation analyses will be performed for this objective. The correlation between the different CS measurements is expected to be weak as reported on associations between certain CS measures and tests.^24^ For a correlation coefficient of 0.25, an α error probability of 0.05 and a power of 0.8, a minimum sample size of 97 is calculated.
*Sample size for objective 2: to analyse whether reference symptoms and signs attributed to CS are associated with functioning measurement outcomes; and for objective 3: to analyse whether changes (between baseline and discharge) in reference symptoms and signs attributed to CS are related to changes in each of the functioning measurement outcomes*. Multiple regression analyses will be performed for objectives 2 and 3. Based on the associations between CSI and psychosocial and cognitive behavioural factors,^24 25^ the effect size is hypothesised to be medium. Since minimally three CS measurements are tested with sex and age required as independent variables, and controlled for the confounding effect of other demographic and test-related variables, eight predictors are foreseen. Taking into account the factors mentioned above, the sample size calculation results in a minimum of 77 patients, calculated with an α error probability of 0.05 and a power of 0.8. Finally, patients measured at discharge could be about 30% less than at baseline due to either not following the interdisciplinary rehabilitation programme or personal reasons; a sample size of 110 patients may be required in this scenario.

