The presence of missing data will be checked. If a variable has more than 10% of missing data cases, its distribution will be further examined. When the distribution of missing data is missing completely at random, analyses with pairwise deletions are planned. If data are not missing completely at random, other suitable solutions will be applied such as multiple imputation.^91^ Regarding the presence of outliers, cases at 3 SD from the mean will be considered as outliers. Their influence will be measured using Cook’s distance and leverage values. When the outliers are not statistically influential and/or there is rationale for the outlier, no further actions are planned. The descriptive statistics of the sample characteristics and main test results will be at this point calculated; numerical variables as mean and SD in normally distributed data and as median and IQR (25–75)) in non-normally distributed data, and categorical variables as counts and percentage of each category level.

*Statistical approach for objective 1: to analyse the association between instruments assessing reference symptoms and signs attributed to CS.* Multiple partial correlation analyses will be performed and corrected for potential confounders. CS measurements will be the main variables and sex and age will be covariates. Additional covariates may enter the partial correlations based on their correlation coefficient with CS instruments and if p<0.01. Results will be reported as correlation coefficients (Pearson’s r and/or Spearman’s rho) and p values, with and without controlling for covariates. The significance level for all analyses is established at 0.01, to account for the potential type I error due to the multitude of partial correlation analyses.
*Statistical approach for objective 2: to analyse whether reference symptoms and signs attributed to CS are associated with functioning measurement outcomes.* First, multiple correlation analyses, followed by multiple regression analyses with data obtained at baseline, will be performed. Each of the main outcomes from functioning measurements will be introduced in the models as dependent variable, CS measurements as independent variables, and sex, age and other demographic characteristics and/or test-related variables as potential confounders and/or moderators.

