*Statistical approach for objective 3: to analyse whether changes (between baseline and discharge) in reference symptoms and signs attributed to CS are related to changes in each of the functioning measurement outcomes.* A similar approach to objective 2 will be performed: first, multiple correlation analyses will be performed with data obtained at baseline and discharge, followed by multiple correlation analyses using delta scores of the data and, finally, multiple regression analyses again using delta scores. As in objective 2, each of the main outcomes from functioning measurements will be introduced in the models as dependent variable, CS measurements as independent variables, and sex, age and other demographic characteristics and/or test-related variables as potential confounders and/or moderators.

Confounders entering the final models of objectives 2 and 3 will be selected based on their partial correlation coefficient with CS and functioning, and they will be included if p≤0.10. All multiple regression models will have the assumptions checked. Results of objectives 2 and 3 will be reported as coefficient (b), CIs (95% CI), p values and explained variance, with and without controlling for confounders and/or moderators. Due to the large amount of correlation analyses and the risk of high type I error, a stricter significance level for correlation analyses is established, p<0.01. For multiple regression analyses the significance level is at 0.05.

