There are circumstances that might have influenced the results, in spite of the team’s efforts to obtain the most extensive insights of CS and its association with functioning. To begin with, it should be considered that patients participating in the study are volunteers. Moreover, the exclusion criteria, despite being based on patients’ files, are also dependent on doctor’s judgement. The impact of these circumstances is so far unknown to the authors. Likewise, given the CAU design of the study the choice of measurements has to be feasible and compatible with the regular clinical procedures. As a consequence, the functional MRI, a commonly mentioned instrument to measure CS, could not be performed in the study. The HRV, on the other hand, although less often used, can be an insightful and innovative approach to the assessment of one of the indicators of CS. Additionally, the sample sizes are estimated a priori for the analyses due to insufficient previous studies and, therefore, they are of exploratory nature and used as a guide. Also, despite the efforts of the team to promote the study participation and participant retention, it is likely that patient recruitment may be slower than anticipated and that the patient may not have a complete follow-up. However, since the measurement period is ample, the calculations are vigilantly made with generous margins (see the Methods and analyses section, Sample size), and the literature related to the topic has shown smaller sample sizes.^25 28 110^ We remain positive about the sample size and expect to have more than enough participants to perform analyses with sufficient power. Also, for comparability purposes, measurements are planned to take place within 3 weeks from the Pain Rehabilitation team’s baseline and discharge assessments. The CSI, PDI and psychological screening questionnaires during baseline assessment are sent to be filled up 6 weeks before the rest of the measurements are obtained, a time distance due to waiting list time. Measurements are expected to be comparable to the rest of measurements at baseline, since no important changes are foreseen in patients regarding medication, surgery or personal conditions during this time, and questionnaires have shown to have good clinimetric properties. As opposed to the limitations presented, given the large amount of correlations in the multiple correlation analyses and the risk of type I error, a more strict significance level was applied, that is, 0.01. Also, for the QST the proxy will be selected per functioning outcome to obtain the most informative somatosensory measurement for each of the functioning measurements. We are confident that the results obtained will provide meaningful and valuable information.

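### Objective 1 is sized at alpha 0.05 (97 patients, a one-sided figure) but tested at 0.01, so the stated 80% power is not reached on either sidedness

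*Protocol article*

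**What the plan says.** The Sample size section of the protocol article gives objective 1 its own calculation. The effect is fixed by "For a correlation coefficient of 0.25", and the error rates and the result follow: "an α error probability of 0.05 and a power of 0.8, a minimum sample size of 97 is calculated". Sidedness is not given.

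The Analyses section, in its paragraph on objective 1, plans partial correlations between the central sensitisation measures, with sex and age as covariates and others added if they qualify. It then sets the threshold: "The significance level for all analyses is established at 0.01, to account for the potential type I error due to the multitude of partial correlation". For the correlations in objectives 2 and 3 the same level is repeated: "a stricter significance level for correlation analyses is established, p<0.01". Sidedness is again not given.

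The Objective(s) section words objective 1 as an association between the three instruments, without a direction. The overall target of 110 is derived in the Sample size section from the regression figure of 77 with about 30% loss by discharge, not from objective 1. The sample sizes are called exploratory there and again in the Discussion. The Discussion nevertheless describes the calculations as made with ample margin and says that the team "expect to have more than enough participants to perform analyses with sufficient power".

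**The concern.** The alpha in the sample size calculation is not the alpha in the analysis. Moving from 0.05 to 0.01 costs a good deal of power at a correlation as small as 0.25, and the calculation was not redone. The figure of 97 also looks low for a two-sided test at 0.05, which suggests that it came from a one-sided calculation that the text does not declare.

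Objective 1 asks whether three instruments that may reflect the same phenomenon are associated. If the true correlation is the one that the protocol assumes, a test with roughly even odds of detecting it says little when it comes out non-significant. A reader who trusts the stated 80% power could give such a result more weight than it deserves.

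**Working it through.** **Inputs.** r = 0.25 against 0, alpha 0.05, power 0.80 and n = 97 (Sample size, objective 1); alpha 0.01 (Analyses, objective 1); overall target 110 (Sample size, objectives 2 and 3). Sidedness is not stated, so both are shown.

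**Formulas (Fisher z).** With atanh(0.25) = 0.2554:

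- Required n = ((z_alpha + z_power) / 0.2554)² + 3, with z_power = 0.8416.
- Power ≈ Φ(0.2554 × √(n − 3) − z_alpha).

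**Step 1: reproduce the 97.**

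- One-sided 0.05: ((1.6449 + 0.8416) / 0.2554)² + 3 = 97.8.
- Two-sided 0.05: ((1.9600 + 0.8416) / 0.2554)² + 3 = 123.3.

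The exact bivariate-normal distribution of r gives 97 one-sided (power 80.1%) and 123 two-sided. So the stated figure reproduces, but only one-sided. With a two-sided test at 0.05, n = 97 gives 70.2% power (exact).

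**Step 2: required n at the planned 0.01.**

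- Two-sided: ((2.5758 + 0.8416) / 0.2554)² + 3 = 182.0.
- One-sided: ((2.3263 + 0.8416) / 0.2554)² + 3 = 156.8.

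The exact method gives 182 and 157.

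**Step 3: power at 0.01 for r = 0.25.**

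- n = 97: 0.2554 × √94 = 2.476. Two-sided: Φ(2.476 − 2.576) = 46.0%. One-sided: Φ(2.476 − 2.326) = 56.0%.
- n = 110: 0.2554 × √107 = 2.642. Two-sided: Φ(2.642 − 2.576) = 52.6%. One-sided: Φ(2.642 − 2.326) = 62.4%.

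| Alpha and sidedness | n for 80% power (exact) | Power at n = 97 (exact) | Power at n = 110 (exact) |
|---|---|---|---|
| 0.05 one-sided | 97 | 80.1% | 84.4% |
| 0.05 two-sided | 123 | 70.2% | 75.6% |
| 0.01 one-sided | 157 | 56.3% | 62.7% |
| 0.01 two-sided | 182 | 46.2% | 52.8% |

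A noncentral-t calculation agrees within about one percentage point of power and three patients.

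**Step 4: covariates and missing data.** Partialling out sex and age lowers the two-sided 0.01 power to 45.2% (n = 97) and 51.9% (n = 110). The figures for 110 assume that objective 1 uses baseline data and that every patient has both measurements. The Measurements section already foresees missing values for the wind-up ratio and for dynamic allodynia at locations where the single stimulus is rated 0. Some correlations may therefore rest on fewer patients; the documents do not say how many.

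**Step 5: what 110 patients can detect.** Two-sided 0.01 with 80% power: tanh((2.5758 + 0.8416) / √107) = tanh(0.330) = 0.32.

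**Step 6: precision.** An observed r of 0.25 with n = 110 has a 95% confidence interval of tanh(0.2554 ± 1.96 / √107) = 0.07 to 0.42.

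**The case against.** Several things can be said for the plan.

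*The arithmetic is sound.* A reader might infer from the gap between 97 and 123 that the sample size was miscalculated. That is not supported: 97 is right for a one-sided test at 0.05. The faults are that the sidedness is not stated and that the alpha does not match the analysis.

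*Sidedness is open in the analysis too.* A reader might take 46% to 53% as the one true power. The documents do not settle that. Objective 3 says which direction on each instrument means less sensitisation, so a directional test for objective 1 cannot be ruled out, although objective 1 itself names none. The one-sided range of 56% to 63% belongs beside the two-sided one. This widens the answer but does not rescue the 80%.

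*The sample sizes are labelled exploratory.* They are, twice. 97 is called a minimum and 110 is not a cap. That lowers the stakes in an observational correlation study. But the label is explained by the scarcity of earlier studies, which concerns the assumed effect. It does not reconcile two different alphas, and the Discussion goes beyond it when it expects sufficient power.

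*No misreading is planned.* A reader might infer that non-significant correlations will be reported as proof that the instruments are unrelated. The documents do not say so. The plan expects weak correlations, regards the instruments as complementary and will report coefficients as well as p values. The risk is that such a reading could occur.

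*The Discussion's assurance is general.* It covers all objectives, so the point requires only that it be narrowed.

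It may also be tempting to recover power by testing just three between-instrument correlations with a stepwise correction. The plan does not define such a family: quantitative sensory testing comprises six tests, and no single variable from it is predefined. The step would also loosen a threshold set deliberately for multiplicity.

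**Conclusion.** The point stands as an inconsistency between sizing and analysis. The 80% power stated for objective 1 belongs to a one-sided test at 0.05. At the planned 0.01 and the assumed r = 0.25, power falls short of 80% by about 27 to 34 percentage points if the tests are two-sided (110 and 97 patients) and by about 17 to 24 points if they are one-sided.

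The two-sided figures rest on an assumption: the article never states sidedness, and two-sided is simply the natural reading of an objective that names no direction. All figures are for a single correlation under bivariate normality with complete data. Covariates and missing values make them slightly to somewhat worse. The conclusion that 80% is missed at 0.01 does not depend on the sidedness, nor on whether 97 or 110 patients are analysed.

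**What to change.** In the Sample size section, state the sidedness and say that 97 is a one-sided 0.05 figure. Restate the power of objective 1 for the planned 0.01 test. If two-sided, with 110 patients and complete data: about 53% for r = 0.25, and a smallest correlation detectable with 80% power of about 0.32. Note that both are slightly worse after partialling out covariates or with missing data. If the tests are meant to be one-sided, say so and give about 63% for r = 0.25 instead.

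In the Discussion, limit the statements on ample margins and sufficient power so that they do not cover objective 1.

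In the Analyses section, add 95% confidence intervals to the objective 1 correlations, as is already planned for the results of objectives 2 and 3, so that a non-significant result is not taken as absence of association.

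The cost is wording and one extra column in the results. The stated power becomes less favourable. No patients are added and the 0.01 threshold stays as it is.

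### The 77 patients and 80% power for objectives 2 and 3 fit a joint test of three CS variables, but the analysis section describes only per-coefficient inference, to which the 80% does not carry over

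*Protocol article*

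**What the plan says.** **Sample size section, objectives 2 and 3.** The effect is given in words only: "the effect size is hypothesised to be medium". Its source is described as "Based on the associations between CSI and psychosocial and cognitive behavioural factors". The structure of the model follows: "Since minimally three CS measurements are tested with sex and age required as independent variables", plus further confounders, so that "eight predictors are foreseen. Taking into account the factors mentioned above, the sample size calculation results in a minimum of 77 patients". The error rates are "calculated with an α error probability of 0.05 and a power of 0.8". An allowance of about 30% for patients not measured at discharge takes 77 to 110.

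**Analyses section, objectives 2 and 3.** There is one regression per functioning outcome, with the CS measurements as independent variables. On output: "Results of objectives 2 and 3 will be reported as coefficient (b), CIs (95% CI), p values and explained variance". These are given with and without the confounders or moderators. On the error rate: "For multiple regression analyses the significance level is at 0.05". No test of the CS variables as a group is named.

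**Sex and age.** The Sample size section says of them that "all analyses will include these variables for a moderator effect". The Abstract says the regressions are corrected for them. The Analyses section makes them covariates for objective 1, and possible confounders or moderators for objectives 2 and 3.

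**The concern.** A power figure belongs to one hypothesis test. The sample size describes three tested variables within a model of eight, which is a block test. The analysis section describes separate p values for each coefficient. Its only with/without comparison removes the confounders and moderators and leaves the CS variables in, so it does not supply the block test.

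The objectives name each instrument separately, so readers will judge CSI, QST and HRV by their own p values. If they also believe those tests have 80% power, they may read a non-significant coefficient as evidence that the instrument is unrelated to functioning, when the test may have had about an even chance of detecting its share of the effect.

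The unsettled role of sex and age adds a problem of interpretation. Once a CS variable is multiplied by sex or age, its own coefficient is no longer the overall association that the objective asks about.

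**Working it through.** **Inputs.** Alpha 0.05, power 0.80, three tested CS variables, eight predictors, 30% loss and a target of 110 all come from the Sample size section. Assumption: medium means f² = 0.15. The document gives no number, but this value reproduces its result.

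**Formula.** With u tested predictors out of p in the model, the F test has u and N − p − 1 degrees of freedom and noncentrality λ = f² × N. Power is the probability that the noncentral F exceeds the central F critical value at alpha 0.05.

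**Step 1: reproduce 77.** For u = 3, p = 8, N = 77: denominator df = 77 − 8 − 1 = 68, λ = 0.15 × 77 = 11.55, power = 0.800. The other eight-predictor tests do not give 77:

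| Tested predictors of 8 | N for 80% power |
|---|---|
| 1 | 55 |
| 2 | 68 |
| **3** | **77** |
| 4 | 85 |
| 5 | 92 |
| 8 (overall test) | 109 |

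The number tested drives the result; the total matters little (3 of 5 also gives 77). The loss allowance is right: 77 / 0.7 = 110.

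**Step 2: power for one coefficient.** Now u = 1, p = 8, with denominator df 68 at N = 77 and 101 at N = 110. The block effect of 0.15 has to be divided among the three variables, and the document does not say how.

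| f² carried by the coefficient | λ at 77 | Power at 77 | λ at 110 | Power at 110 |
|---|---|---|---|---|
| 0.15 (all of it) | 11.55 | 0.918 | 16.5 | 0.981 |
| 0.075 (half) | 5.775 | 0.659 | 8.25 | 0.812 |
| 0.05 (equal thirds, uncorrelated) | 3.85 | 0.490 | 5.5 | 0.642 |
| 0.03 (equal effects, pairwise correlation 0.25) | 2.31 | 0.322 | 3.3 | 0.436 |

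The last row takes equal standardised coefficients, all coded in the same direction, and borrows the 0.25 that the article expects between CS measures in objective 1. The block effect is proportional to 3 + 6 × 0.25 = 4.5. The share of one variable's variance explained by the other two is 2 × 0.25² / 1.25 = 0.10. The unique effect is therefore 0.15 × 0.90 / 4.5 = 0.03.

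A coefficient needs f² of about 0.10, two thirds of the block effect, to come close to 80% at n = 77 (power 0.781; N = 81 for 80%). With f² = 0.05, 80% power needs N = 160.

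**Step 3: the joint test at the baseline target.** For u = 3, p = 8, N = 110: λ = 16.5, power = 0.932.

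**Step 4: effect of moderator terms on the joint test.** Three CS variables times sex and age would add 3 × 2 = 6 products, giving 14 predictors. If they are in the model but not tested (3 of 14), power at 77 is 0.798 and the required N is 78.

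**The case against.** The best defence is that the sample size is correct and fits its own description: three tested of eight gives 77 exactly. The article condenses a fuller plan, lists explained variance among the results, and excludes no R² change test. A reader might infer that the joint test will never be run. The document supports only that it is not named. It also calls the sample sizes exploratory and a guide, although the Discussion still expects sufficient power.

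A second defence is that the effect size was drawn from associations of one instrument, the CSI. If f² = 0.15 applied to each coefficient, 77 would give 92% power and be conservative. That is possible, and it is why no single lower figure can be asserted. But a single-coefficient calculation with 0.15 would have given 55. The stated 77 commits 0.15 to the block of three.

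Three stronger readings are tempting and not supported:

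- **That per-coefficient power is 49%.** This holds only for an equal split among uncorrelated variables, at the discharge sample size. Objective 2 uses baseline data with a target of 110.
- **That uncounted moderator terms invalidate the power.** As untested terms they cost 0.002. Power would fall to 0.571 at n = 77 (N = 114 for 80%) only if the six products were tested together with the three CS variables (9 of 14), which the document does not propose. The six products are themselves inferred from inconsistent wording.
- **That 3 × 4 × 2 = 24 coefficients at 0.05 give a 71% chance of a false positive** (1 − 0.95²⁴ = 0.708). This assumes independent tests. The variables come from the same patients, and multiplicity is a separate question from the one here.

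**Conclusion.** The mismatch is real and limited. The 77 is a correct sample size for a joint 3-df test of the CS block. The article names no such test and describes inference coefficient by coefficient, so its 80% does not apply to the tests it describes.

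How far single-coefficient power departs from 80% depends on an unstated division of the effect. At n = 77 it runs from 92% down to about 32% over the cases computed. At n = 110 the corresponding range is 98% down to 44%. All of this rests on f² = 0.15; the equal split and the 0.25 correlation are further assumptions.

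The inconsistent role of sex and age needs settling so that the coefficients can be interpreted. It does not materially change the power of the joint test.

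**What to change.** 1. In the Sample size section, name the test (F test of the R² increase, three tested of eight predictors) and the numeric f².
2. In the Analyses section, answer each outcome's question in objectives 2 and 3 by the 3-df R² change F test when CSI, RMSSD and one QST variable are added to the covariates. Fix the QST variable in advance. At present it is chosen by its correlation with each functioning measure, and the F test does not allow for that selection.
3. Treat single coefficients as secondary to the joint test.
4. State that the 80% applies to the joint test only, and give per-coefficient power as a range with its assumptions, such as the table above, rather than as one figure.
5. Enter sex and age as covariates in the main model. Put any interactions with them, centred, in a separate secondary model, and align the wording across sections.

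The cost is some rewording and one extra F test per model, with no change to recruitment. The small downside is that claims about a single CS instrument become secondary.
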